Active monitoring has been described as a decision “between the clinician and the patient to not treat the condition and to intermittently reassess its status along some rational time course in follow-up” [14]. According to the Catalan guideline [13], for patients receiving active monitoring, the GP should monitor the patient within 15 days of the first visit. Other recommendations are to accompany closed monitoring with low intensity psychosocial therapy (e.g. problem-solving techniques, counselling or brief CBT), individual guided self-help programs based on CBT or structured and supervised exercise programs of moderate intensity. The guidelines only recommend the use of antidepressants in mild major depression if the patients have a history of moderate or severe episodes of depression or if they have other medical conditions or associated comorbidities.

Despite being recommended in guidelines, the effectiveness of active monitoring has not been proven conclusively. There has been a study showing a low likelihood of spontaneous remission in minor depression following a one-month active monitoring period in primary care. However, the same study showed that engaging in regular pleasant activities conferred an advantage to remission in minor depression.. The study recommended the use of feasible interventions that promote activity and decrease avoidant coping styles in primary care [14]. Furthermore, an economic evaluation of usual GP care with or without antidepressant medication for patients with minor or mild-major depression observed no differences in cost-effectiveness between the two treatment strategies, recommendeding that GPs sparingly prescribe antidepressants to mildly depressed patients [15]. On the contrary, in older primary care patients with dysthymia and minor depression, a problem-solving behavioral based psychotherapy in primary care showed smaller benefits for depressive symptoms than paroxetine [16]. More recently, the THREAD study compared selective serotonin reuptake inhibitors (SSRIs) plus supportive care versus supportive care alone for mild to moderate depression with somatic symptoms in primary care [17]. The study showed that adding an antidepressant was more cost-effective than supportive care alone.

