### Study setting and GP enrolment

GP enrolment was conducted six months before patient recruitment. GPs from the province of Barcelona were invited to participate. The University Institute in Primary Care Research Jordi Gol (IDIAP Jordi Gol), which gives technical support to every professional that works in Primary Care in the Catalan Public Health System, spread the invitation to participate in the study to all the GPs from the province of Barcelona. Furthermore, the research team contacted the Primary Care Centers with whom they had worked in previous research studies to invite them to participate.

The study is conducted in 12 primary care centers in the province of Barcelona (Spain). The participating centers have between six and 17 primary care teams (each of them consisting of a GP and a nurse) and attend to a population of 250,000 to 350,000 inhabitants. Sixty-eight GPs participated in the recruitment of patients for the study.

Prior to the study, GPs received a three hour-training on the study protocol, diagnostic criteria for depression, and national guidelines for the treatment (pharmacological and non-pharmacological) of MDD in primary care, divided into two 1.5-hour sessions. Session 1: Diagnosis and non-pharmacological treatment for MDD (active monitoring, sleep hygiene, counseling, frequency of follow-up visits, health education and low intensity psychological therapies); and Session 2: pharmacological treatment of MDD. During the study, a monthly newsletter is sent to the participating GPs to remind them of the topics presented in the training seminars and to inform them about the study progress.

At the beginning of the study, the GPs completed a questionnaire collecting the following variables: sociodemographic characteristics, job characteristics, training, attitude towards depression, interest on mental health and participation in communication groups [20].

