### Interventions

This is a naturalistic study. GPs use their professional clinical judgment to recommend a treatment option to the patient. GPs can recommend a non-pharmacological intervention (Active Monitoring Group) or a pharmacological treatment with antidepressants (Medication Group) following their own clinical criteria and experience.

The patients in the Active Monitoring Group receive the usual treatment that the GPs perform when applying active monitoring without a pharmacological treatment. According to the Catalan guideline [13], which has been presented to all the GPs, active monitoring requires a first follow-up visit within the following 15 days. Afterwards, it recommends from six to eight follow-up visits over 10–12 weeks, where the GPs can consider low intensity psychosocial therapies such as counseling, problem-solving techniques or on-line CBT. Also, it recommends structured and supervised exercise programs of moderate intensity. As part of the stepped care model, in case the patient’s condition does not improve, the GP can intensify the treatment and initiate antidepressants.

Adherence to active monitoring is controlled through patient interviews (patients are asked the number of control visits with the GP and the recommendations to deal with depression from their GP). Also, at the end of the study, the GPs will be asked to describe the actions that were taken with patients in the Active Monitoring Group.

The patients in the Medication Group recieve the antidepressants usually prescribed in Spanish primary care at doses usually recommended according to their symptoms and characteristics. The national guidelines recommend initiating a pharmacological treatment with SSRIs (particularly with citalopram, sertraline, paroxetine or fluoxetine) in accordance with the Catalan Health Service’s recommendations following cost-effectiveness criteria [13].

Adherence to antidepressants is monitored through two methods: pharmacy records (computerized pharmacy records that register information about medication including active principle, dose and units supplied in the patient’s clinical history at the time of purchase), and patients’ self-reported adherence (with the 4-item scale developed by Morisky and colleagues [21]).

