At the moment of patient inclusion, GPs complete a form that includes the following information: patient allocation (active monitoring or antidepressants) and reasons for the allocation and type and dose of antidepressant prescribed, if any. Withdrawal or changes in treatment and the reasons (initiation of antidepressants or changes in active principle) will be registered in another form. This will allow the evolution of treatment in naturalistic conditions to be monitored.

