### Propensity score calculation

The allocation of patients is done according to the GP’s decisions. Thus, it is expected to have bias, as groups could not be comparable. To minimize the bias resulting from the lack of randomization, we will use a propensity score. First, it will be evaluated where the probability of receiving active monitoring or antidepressants is affected by GP factors (socio-demographic characteristics, job characteristics, training, attitude towards depression, interest on mental health and participation in communication groups) and/or patient factors (socio-demographic characteristics, baseline severity of depression, presence of major depression according to SCID-I criteria, severity of anxiety, comorbid conditions and beliefs about medicines). Second, a logistic regression model will be used to calculate a propensity score. The dependent variable of this model will be the group (active monitoring or antidepressants) and the independent variables will be those that are associated with a higher or lower probability of receiving active monitoring or antidepressants.

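### A history of moderate or severe depressive episodes, which the protocol gives as a guideline ground for antidepressants in mild MDD, is not listed for the propensity score, so its control is not assured

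*Protocol article*

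**What the plan says.** All references are to the protocol article.

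- **Allocation.** There is no randomisation: "GPs use their professional clinical judgment to recommend a treatment option to the patient" (Interventions).
- **Guideline grounds.** The Background section reports: "The guidelines only recommend the use of antidepressants in mild major depression if the patients have a history of moderate or severe episodes of depression". Comorbidity or another medical illness is the alternative ground. No other ground is given for mild cases.
- **What the GPs were told.** Their training before the study covered "national guidelines for the treatment (pharmacological and non-pharmacological) of MDD in primary care" (Study setting and GP enrolment). The Interventions section adds: "According to the Catalan guideline [13], which has been presented to all the GPs".
- **Who is eligible.** Patients need a new episode of MDD, not a first one. Antidepressant use is an exclusion only if it falls within the previous 60 days (Eligibility criteria and recruitment).
- **Propensity score.** The patient factors are socio-demographic characteristics and "baseline severity of depression, presence of major depression according to SCID-I criteria, severity of anxiety, comorbid conditions and beliefs about medicines". From the factors examined, "the independent variables will be those that are associated with a higher or lower probability of receiving active monitoring or antidepressants".
- **Outcome models.** All are adjusted for gender, age and the propensity score. Other baseline variables thought relevant are tested by likelihood ratio tests (Incremental cost-effectiveness ratios calculation).
- **Recorded reasons.** At inclusion the GP's form captures "patient allocation (active monitoring or antidepressants) and reasons for the allocation" (Interventions).

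**The concern.** By the protocol's own account, a past moderate or severe episode is something a guideline-trained GP would weigh when deciding whether to prescribe for a mild case. The list for the score includes one of the two guideline grounds and omits the other. The rule for building the score screens the factors examined, so a factor that is not on the list is never screened.

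If past episodes also worsen the 12-month course or raise costs, medication patients would carry more recurrent illness than active-monitoring patients with the same score. Antidepressants would then look less effective, and possibly more costly, than they are. The incremental effects, the incremental costs and the acceptability curves would all carry that distortion.

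**Working it through.** **1. Guideline grounds against the list**

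| Guideline ground (Background) | In the propensity list? |
|---|---|
| Other medical conditions or comorbidity | Yes, as comorbid conditions |
| History of moderate or severe episodes | No |

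**2. Does history vary between patients?** Yes. Recurrent cases are eligible, and the 60-day antidepressant exclusion does not remove them.

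**3. Does a listed factor stand in for it?** Not directly. Baseline severity and the SCID-I diagnosis, as the protocol uses them, describe the current episode. The comorbidity measure described under Outcomes and participant timeline is a check-list of chronic physical conditions. No section names previous episodes as a collected variable.

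**4. Does another analysis catch it?** The outcome models might, if history is available, is judged relevant and passes the likelihood ratio test. The listed sensitivity analyses do not. Changing perspective or wage, analysing per protocol, dropping the score, or restricting to DSM-IV cases adds no adjustment for history.

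**5. Scale.** The protocol gives no figure to reproduce: the sample size of 150 per arm comes without an effect size or SD. The following inputs are therefore assumptions:

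- residual difference in prevalence of prior episodes between groups, after adjustment for the listed factors: 10 to 30 percentage points;
- effect of such a history on 12-month PHQ-9: 1 to 3 points;
- SD of PHQ-9 at 12 months: 5 to 6 points.

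Bias = residual prevalence gap × effect of history on the outcome:

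| Gap | 1 point | 2 points | 3 points |
|---|---|---|---|
| 0.10 | 0.1 | 0.2 | 0.3 |
| 0.20 | 0.2 | 0.4 | 0.6 |
| 0.30 | 0.3 | 0.6 | 0.9 |

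Standard error of a simple difference with 150 per arm = SD × √(2/150) = SD × 0.1155:

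- SD 5: 0.58 points
- SD 6: 0.69 points

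The smallest bias, 0.1, is about 0.14 to 0.17 of a standard error. The largest, 0.9, is about 1.3 to 1.6 standard errors. The standard error ignores drop-out, clustering by GP and covariate adjustment, so it serves only as a yardstick.

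**6. Does resampling help?** No. The bootstrap reproduces sampling variability around whatever the adjusted model estimates. Whether 5,000 replications or more are used, the centre stays where the omitted factor has put it. The same formula applies to QALYs and costs, but the documents give no inputs for either.

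**The case against.** The strongest case on the other side has four parts.

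- **An article condenses.** The full protocol might code history from the clinical interview, and nothing in the list says it is exhaustive. This stands in part: the list need not be treated as closed. But it is a specific enumeration without any wording to mark it as examples, and it takes up one of two paired criteria. That is a mismatch within the article and not merely absent detail.
- **There is a second layer of adjustment.** The outcome models can admit relevant baseline clinical variables. This stands, and a reader who inferred that history is left wholly uncontrolled would go too far. The route commits to nothing, however: history is not named and selection is by a test.
- **The confounding is not demonstrated.** The guideline ground concerns mild depression and past moderate or severe episodes, not any earlier episode. GPs may follow their own criteria, the Background section notes poor adherence to recommendations, and the driver of selection named in the Discussion is current severity, which is in the score. The link with outcome rests only on the Background section's general remark that recurrence and chronicity contribute to expenditure. All of this stands. History is a plausible confounder that the protocol itself points to, not a proven one.
- **The data may not exist.** The SCID-I is described as confirming the diagnosis, pharmacy records are described for adherence and medication use with no look-back period, and the history review is for medication. This stands and makes the cost of the fix conditional.

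A reader might also infer that the bias serves a conclusion the study hopes for. The Discussion does not support that. Its sentence on savings is conditional, and it states the allocation bias openly as a limitation.

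**Conclusion.** The point holds in limited form. The listed propensity factors omit a ground for prescribing in mild MDD that the protocol itself reports, while including its companion, so control of that factor depends on an optional step in the outcome models. The direction, in favour of active monitoring, follows only if history both raises prescribing and worsens prognosis.

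The size of 0.1 to 0.9 PHQ-9 points rests wholly on assumed inputs. It runs from negligible to more than one standard error, so a material bias is possible but not shown. The change is still worth making, because statistical adjustment is all that stands in for randomisation here and neither more patients nor more replications would remove the bias.

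**What to change.** 1. Under Propensity score calculation, add to the patient factors: prior depressive episodes, with severity where recorded, and antidepressant treatment more than 60 days before inclusion.
2. Keep both in the score whether or not they are statistically associated with allocation in the sample, and report their balance between groups after adjustment.
3. Take them from the SCID-I mood module, pharmacy records and patient-history review where these hold the information. If the severity of past episodes is not available, use any prior episode or prior antidepressant use as a proxy and state the limitation.
4. Tabulate the GPs' recorded reasons for allocation and check that each common patient-level reason is represented in the list. Do not enter the reasons themselves in the score, because they may separate the groups.

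The cost is a little extra record extraction and a few lines of analysis text, provided the sources hold the information. That should be confirmed first, since no section of the protocol establishes it.

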### Incremental cost-effectiveness ratios calculation

Incremental effects and costs between groups will be modelled using generalized linear models. First, different distribution families and link functions will be tested and Akaike and Bayesian information criterion (AIC and BIC) will be used to decide the model that best fits the distribution of the effects (QALYs and severity of depression) and costs. Second, to select adjustment variables, socio-demographic and baseline clinical variables considered to be relevant will be tested in the models using likelihood ratio tests. All the models will be adjusted for gender, age and the propensity score. Difference in costs and effects will be calculated using the final models in each of the imputed databases and combined as per Rubin’s rules [40]. Incremental cost-effectiveness ratios will be calculated by diving the difference in costs between groups by the difference in effects.

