### Sample size

In cost-effectiveness studies, sample size calculations have been criticized and their usefulness has been questioned [42]. This calculation is influenced by many parameters, some of them related to costs, which must be specified a priori. However, knowledge about costs and deviations is scarce so it is required to make assumptions that affect the calculation of the sample size. Moreover, this calculation requires to decide, in advance, what the maximum acceptable incremental cost-effectiveness ratio or maximum willingness to pay will be. Again, where to put the cutoff points for these parameters is a complicated decision. Finally, it should be borne in mind that the results of the economic evaluation will be presented in cost-effectiveness acceptability curves. These curves are not based on statistical inference so the meaning of sample size calculations could be questioned again.

On the other hand, to deal with the uncertainty in the sampling distribution of the incremental cost-effectiveness ratio, it will be necessary to perform resampling techniques that require a minimum sample size. Previous experience in these randomized studies with naturalistic conditions indicates that a total of 150 patients per arm will suffice [41,43].

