## Discussion

The results of this study will provide evidence about whether active monitoring in mild-moderate MDD can be a feasible and cost-effective alternative to pharmacological interventions in actual practice primary care. Although clinical practice guidelines recommend active monitoring, evidence of its effectiveness and efficiency is scarce and contradictory. This study will improve knowledge on active monitoring efficiency and, as far as is known, it will be the first study on this topic to be conducted in Spain. If non-pharmacological interventions would prove to be more cost-effective than pharmacological ones, this would show that preventing the use of antidepressants in patients with mild-moderate MDD could save the health care system money and protect patients from side-effects of non-necessary drugs.

The study has a series of limitations that must be considered. The naturalistic nature of the study implies the use of wide inclusion criteria and non-randomized group assignment, which increase the external validity of the results. However, wide inclusion criteria can increase the inter-subject variability and reduce the ability to detect differences. It is more likely for the GP to allocate patients presenting with mild depression to the active monitoring group than to the pharmacological treatment group. Conversely, for patients with moderate-severe depression, GPs might be more likely to choose pharmacological options than active monitoring. Propensity score techniques will be used to try to minimize the impact of this bias in the results of the study.

One limitation of the study is the GP selection. The group of GPs that decided to participate in the study could have a greater interest in mental health. This might include specific attitudes of those GPs when facing physiological problems in primary care and might not represent average GP behavior. Along these lines, it is possible in this study that GPs enroll patients that they think that will be more willing to participate and remain in the study. Also, all the health centers are located in the same health area, so the intervention can be biased for specific practices associated to local culture or characteristics of the health system.

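### The propensity score takes its variables by association with treatment group instead of expected relation to cost and outcome; the harm left after the outcome-model step is conditional and moderate

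*Protocol article*

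**What the plan says.** Under Propensity score calculation, the Protocol article sets out two steps. First, it examines whether the choice of treatment is "affected by GP factors" (six families of GP characteristics) or by patient factors: socio-demographics, "baseline severity of depression, presence of major depression according to SCID-I criteria, severity of anxiety, comorbid conditions and beliefs about medicines". Second, it fits a logistic model for group in which "the independent variables will be those that are associated with a higher or lower probability of receiving active monitoring or antidepressants". No outcome-related criterion is stated, and GP characteristics are candidates on the same footing as patient prognosis.

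Under Incremental cost-effectiveness ratios calculation, a separate selection is made in the cost and effect models: "socio-demographic and baseline clinical variables considered to be relevant will be tested in the models using likelihood ratio tests". In addition, "All the models will be adjusted for gender, age and the propensity score".

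The Discussion expects severity to drive allocation, since it is "more likely for the GP to allocate patients presenting with mild depression to the active monitoring group", and names propensity score techniques as the means of limiting that bias. The listed minimum of sensitivity analyses includes one without the score, but none with a different covariate set. On size, the Sample size section says that "a total of 150 patients per arm will suffice".

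**The concern.** A propensity score removes confounding by balancing variables that affect the outcome. How well it predicts treatment is not the aim. Choosing its variables by association with group can go wrong in two ways.

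- It can keep a factor that moves allocation but has no path to cost or outcome (an instrument). Such a factor removes no confounding, inflates the variance of the adjusted difference, and amplifies bias from anything unmeasured.
- It can drop a factor that predicts outcome well but allocation only modestly. Such a factor is a real confounder, yet at this sample size it will often fail a test of association with group.

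Allocation is by GP judgement, and the score is the plan's named protection against confounding by indication. The adjusted cost, QALY and PHQ-9 differences, and every ratio and acceptability curve built on them, pass through it.

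**Working it through.** **The plan's own figure.** The size of 150 per arm (2 × 150 = 300) is justified by previous experience, with no inputs to reproduce. It is used here only as n.

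**Hand check of the screen.** The protocol gives no threshold, so p < 0.05 is assumed. For a standardised covariate and equal groups, SE(log-odds ratio) ≈ 1/√(n × 0.25) = 1/√75 = 0.115. An assumed log-odds ratio of 0.15 gives z = 0.15/0.115 = 1.30, so the chance of passing is about Φ(1.30 − 1.96) ≈ 0.25. About 3 of 4 such confounders would be left out of the score.

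**Simulation.** 1,000 runs per setting, n = 300, 68 GPs (Study setting and GP enrolment), true effect 0, residual SD 1. All coefficients are assumptions:

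- severity: log-odds ratio 0.6 on allocation, 0.5 on outcome;
- four modest confounders: 0.15 on allocation, 0.3 on outcome;
- two pure outcome predictors: 0.4 on outcome;
- four GP-level factors acting on allocation only: 0, 0.4 or 0.7;
- one unmeasured confounder: 0 or 0.4 on both.

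The plan's rule (univariate p < 0.05 against group) is compared with a score built on all outcome-related covariates. Each score enters a linear outcome model on the logit scale.

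*Score alone, no unmeasured confounder (plan's rule / outcome-based score):*

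| GP log-odds ratio | Modest confounders dropped, of 4 | Bias | SD |
|---|---|---|---|
| 0 | 3.13 | 0.103 / 0.002 | 0.147 / 0.124 |
| 0.4 | 3.23 | 0.111 / 0.006 | 0.159 / 0.124 |
| 0.7 | 3.43 | 0.119 / −0.002 | 0.177 / 0.122 |

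This is not the planned analysis, because the protocol adds the likelihood ratio step. That step was coded as testing the severity, confounder and predictor variables at p < 0.05.

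*Score plus likelihood ratio step (plan's rule / outcome-based score):*

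| GP log-odds ratio | Unmeasured | SD | Ratio | Bias | Ratio |
|---|---|---|---|---|---|
| 0 | 0 | 0.124 / 0.124 | 1.00 | 0.003 / 0.002 | – |
| 0.4 | 0 | 0.132 / 0.124 | 1.06 | 0.008 / 0.006 | – |
| 0.7 | 0 | 0.143 / 0.122 | 1.17 | 0.002 / −0.002 | – |
| 0 | 0.4 | 0.128 / 0.128 | 1.00 | 0.159 / 0.157 | 1.01 |
| 0.4 | 0.4 | 0.140 / 0.130 | 1.08 | 0.155 / 0.138 | 1.12 |
| 0.7 | 0.4 | 0.152 / 0.131 | 1.16 | 0.151 / 0.112 | 1.35 |

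The Monte Carlo error of a bias is about 0.13/√1000 = 0.004. In variance terms, without unmeasured confounding, the ratios are (0.132/0.124)² = 1.13 and (0.143/0.122)² = 1.37. Raising the modest confounders to 0.25 (GP factors 0.4, nothing unmeasured) left 2.33 of 4 out of the score and gave SD 0.135 / 0.125, a ratio of 1.08.

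**What causes the remainder.** A score holding every candidate, GP factors included, gave SDs of 0.133 and 0.142 after the same step (GP 0.4 and 0.7, nothing unmeasured), against 0.132 and 0.143 under the plan's rule. What remains therefore comes from allocation-only factors in the score. The omitted confounders no longer contribute.

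**What the model leaves out.** It treats every measured confounder as eligible for the likelihood ratio test, uses a linear outcome in place of the planned generalized linear models, and has no clustering of outcome by GP.

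**The case against.** The strongest reply is that the score is not the only adjustment. A reader might infer from the screening rule that strong outcome predictors are lost to the analysis, and that the adjusted differences must be both more biased and less precise. The documents do not support that. Predictors left out of the score can return through the likelihood ratio step, age and gender are always included, and severity is expected to be related to allocation and so to pass the screen. In the simulation the step took bias from 0.10–0.12 to at most 0.008 when nothing was unmeasured. A predictor truly unrelated to group is no confounder in any case; omitting it costs precision only.

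A second tempting reading is that GP training or attitude are instruments. The documents point the other way for training. The Background names lack of psychotherapy knowledge as a barrier to active monitoring, and the Discussion warns that lack of training may turn active monitoring into no treatment. Training or interest in mental health may thus affect outcome and cost, and would then be confounders to keep.

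Both replies stand as limits on size. They do not rescue the rule. The likelihood ratio step covers only variables judged relevant that also pass a test. It does not name GP factors, beliefs about medicines or baseline cost, and it cannot take an instrument out of the score. The missing threshold is a detail for an analysis plan; the criterion of association with group is stated outright.

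**Conclusion.** The point holds as a badly chosen selection criterion with a conditional, moderate cost. If no candidate acts on allocation alone, and the relevant measured predictors are tested in the outcome models, essentially nothing is lost. If some GP factors do act on allocation alone, the SD rises by about 6–8% (moderate) or up to about 17% (strong), and bias from an unmeasured confounder grows by about 12% or 35%. These sizes rest on assumed coefficients, an assumed p < 0.05 for both selections, and a simplified outcome model; only the direction and rough range should be relied on. Any confounder that the likelihood ratio step does not reach would remain unadjusted, by an amount the documents do not allow to be estimated. The listed sensitivity analyses would not reveal either problem, because none varies the score's covariates.

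**What to change.** Replace the association screen with a covariate list fixed in advance by known or expected relation to costs, QALYs and PHQ-9, and keep each variable whatever its association with group.

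- **Patient variables:** socio-demographics, baseline PHQ-9, SCID-I diagnosis, BAI and comorbidity; beliefs about medicines where measured in both groups (the specific section of that questionnaire goes only to the antidepressant group, so it cannot serve); and baseline WHO-DAS, utility and cost where collected.
- **GP variables:** keep a GP factor where it plausibly affects outcome or cost, for example training or interest in mental health, and give the reason. Leave it out otherwise. Do not add fixed GP effects as a substitute: they would condition on every GP-level instrument at once, with 68 GPs for about 300 patients.
- **Checking:** judge the score by standardised mean differences and overlap on all prognostic covariates.
- **Sensitivity:** show the result with and without the GP factors, since whether they are confounders or instruments cannot be settled from the protocol.

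The cost is a change of analysis wording and a little more analysis work. No new data are needed.
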